**Figure 1 fig1:**
[figure not shown]
BEEM project study design.

### Randomization and treatment allocation

Participants are randomized to either the “Phase 1 GI” or “Phase 2 GI” treatment arm by REDCap electronic data capture tools hosted at University of California, San Francisco. REDCap is a secure, web-based software platform designed to support data capture for research studies (53, 54). We loaded REDCap with a randomization sequence generated in SAS software 9.4 (55) using block randomization with varied permutations, with equal allocation to treatment arm and balanced by gender, age group, and city of residence. Due to the nature of the intervention, blinding the participants and study staff is not possible. Study staff inform participants of group assignment during the enrollment appointment, following baseline survey completion. The investigators are blinded to allocation, as is the trial methodologist ([name]), who will run the final analyzes.

### Eligibility and recruitment

Eligible participants must be between 18 and 24 years of age, identify as Black or African-American, have lived in the United States for at least 3 years, have no plans to leave the Bay Area permanently in the next year, not be currently enrolled in another GI project, and live in a Low-Income Housing Tax Credit (LIHTC) Qualified Census Tract (QCT) in San Francisco or Oakland, CA (tracts where 50% of households have incomes below 60% of the Area Median Gross Income (AMGI) or have a poverty rate of 25% of more) (56). Because BEA may live with parents and not know their household income, we utilize the census tract residential criteria as an indicator of low-income, which is standard for recent GI pilots in California. In addition, determination of income can be administratively burdensome for people; using census tracts as a proxy for income-level can reduce barriers for recipients. Given the structural inequities that drive housing access in Black communities, individuals who are unhoused and stay in San Francisco or Oakland are also eligible for participation, pending a letter from an agency serving unhoused young adults that can affirm their housing status.

Eligible participants are recruited from low-income areas in San Francisco and Oakland, CA, two cities with a history of residential segregation and racial economic inequities and which are grappling with gentrification and displacement of Black residents (57). Participants are recruited through partner agency outreach and direct strategies (e.g., flyers, word-of-mouth, street outreach). All interested individuals are directed to a web screening form on a public website;^1^ all those who apply and meet the age, race, and city criteria are asked to provide contact information. They are called or emailed to schedule a phone screening conducted by trained study personnel. After screening, eligible individuals are included in a participant pool. Participants are selected from the participant pool through a monthly, computer-administered drawing balanced by gender, city of residence, and age group (18–20 and 21–24).

### Intervention

The intervention is carried out in partnership with MyPath, a national nonprofit whose mission is to seed and empower economic pathways for low-income youth and young adults, especially Black and Indigenous People of Color (BIPOC). The intervention includes three basic elements: guaranteed income, financial mentoring, and financial capability peer discussion groups–all of which are designed in consultation with community representatives (see Community Working Group described below). The intervention is designed to address multiple levels of influence on health by including components that address not only factors at the individual-level, but also those at the interpersonal-level and, when implemented at scale, community-level factors (see Figure 2). The key ingredient of this approach is that it enables BEA to create a personalized path to build wealth and health. Strategies to address health disparities have traditionally placed the onus on individuals to change. In contrast, GI – with no strings attached – aims to change a structural inequity and eliminates paternalistic indicators of ‘worthiness’ by valuing the autonomy and self-determination of all participants. In the same vein, participation in financial capabilities programming (i.e., financial mentoring and peer-support) in the project is optional and available to participants at any point during the project duration, ensuring that each participant has the right to define what is beneficial for them and when to engage (or not engage) in these options.

**Figure 2 fig2:**
[figure not shown]
Conceptual model of the multi-level black economic equity movement intervention.

#### Guaranteed income (individual and community-level)

An income of $500 is distributed monthly over the course of 1 year, either in their first or second year of the two-year program. The GI distribution will be administered by Community Financial Resources (CFR) via a Focus Card. The Focus Card is a prepaid debit card with no monthly fees, no penalties, and no minimum balance, allowing participants to have immediate access to their funds (akin to a checking account) as well as the ability to save (akin to a savings account). Deposits are made on the first of the month.

#### Financial mentoring (individual-level)

The mentoring component is based on the model at MyPath, which incorporates a racial equity lens and addresses systemic barriers, such as a lack of quality financial products in under-resourced communities. Mentoring includes a blend of services that strengthen financial decision-making skills and access to quality financial products. Mentors are trained and experienced financial coaches with lived experiences that mirrors those of participants. Discussion topics are responsive to each participant and their priorities; however, mentors will ensure that participants understand the ‘basics’ before moving to more complex topics and will have access to a library of topics to support the young people in their varying needs. For example, a participant with a bank account and a budget will not need to review “budgeting and banking 101.” However, if they do not understand credit, the mentor will review this topic before supporting them to move forward with decisions affecting their credit. In past work with BEA, MyPath has identified priority areas, including building credit (credit repair, improving credit scores, credit products); savings (emergency savings plans, savings habits and strategies, understanding savings accounts); money management (creating budgets, understanding income vs. expense, assessing spending, making financial decisions that are aligned with personal goals and values); financial products (credit building products, auto loans, credit cards); and long-term goals (home ownership, investments). Opt-in mentoring sessions are co-scheduled by mentors and participants based on their availability and include up to six one-hour sessions conducted on-line.

#### Peer discussion and support groups (interpersonal-level)

Peer discussion groups, offered twice per month, emphasize financial capability skills and simultaneously create a space for participants to form bonds and seek support on these topics. Consistent with the literature indicating the strengths of peer support groups (58–61) and positive development (62, 63), the discussion groups aim to strengthen social networks and establish cohesion and support as peers reflect on their experiences, share strategies and resources, problem-solve, learn from each other, provide emotional support, hold each other accountable, and experience a sense of belonging. Groups of up to 10 participants are co-facilitated by a financial mentor and a near peer (Black young adult aged 22–27 with extensive financial capability program experience), meet for 1 h, and cover financial content.

### Community working group

All components of the intervention and much of the research design, including the data collection instruments, has been co-designed and is monitored by our Community Working Group (CWG). The CWG is comprised of partnering community agency representatives, city officials involved in health and wealth generation programming, the investigative team, and young adults or near peers. Community involvement was key in selecting a study design that ensured all participants would have access to guaranteed income (that is a wait-list design vs. a standard parallel arms trial). Similarly, the CWG collaborated in the design of the drawing for participant selection–ensuring equity among agency-affiliated and non-agency affiliated participants in that those with fewer connections were not disadvantaged by a first come, first serve model. The CWG also selected the project logo in conversation with the study team and graphic designer and weighed in on the website content and design. The CWG met monthly during project planning and start-up and will meet once every 2 months throughout the remainder of the project. They will also be integrally involved in developing and implementing a dissemination plan, identifying any community concerns with the research, and interpreting and framing the research findings and representation of BEA. CWG members are provided monetary compensation for their participation and time.

### Research hypotheses

Our primary research question is to understand the potential impacts of GI on BEAs investment in their future (education, employment, training), mental health (depressive symptoms), and unmet mental health (MH) and sexual/reproductive health (SRH) service needs. We are also interested in learning if complementary financial supports propel greater impact on health outcomes and understanding to what degree GI impacts dissipate after the transfers end. Thus, our hypotheses are as follows.

*H1*: *GI will improve all outcomes*. Youth receiving GI in phase I will have greater increases in investments in their future (H_1a_), greater decreases in depressive symptoms (H_1b_), and larger reductions in unmet need for MH and SRH services (H_1c_) at 12 months than those who do not received GI in phase I.

*H2*: *GI + financial supports will improve outcomes more than GI alone*. Participants receiving GI in phase I who participate in mentoring or peer discussion groups will have greater increases in investments in their future (H_1a_), greater decreases in depressive symptoms (H_1b_), and larger reductions in unmet need for MH and SRH services (H_1c_) at 12 months than those not opting into financial support programs.

*H3*: *Gains from GI will be sustained*. Participants receiving GI in phase I will not experience a decline in odds of enrollment in educational/training programs (H_3a_) or an increase in odds of depressive symptoms (H_3b_) or unmet need for MH and SRH services (H_3c_) following the removal of GI (between month 12 and 24).

*H4*: *Accessing complementary financial supports prior to receiving GI will improve overall outcomes.* Among BEA who do not receive GI in phase I, those who engage in mentoring or peer discussion groups in phase I will have greater increases in investments in their future (H_4a_), greater decreases in depressive symptoms (H_4b_), and larger reductions in unmet need for MH and SRH services (H_4c_) at 24 months than BEA who did not opt-in into the financial programming prior to receiving GI.

### Data collection and assessments

#### Structured surveys

We conduct comprehensive surveys annually and brief monitoring surveys of primary outcomes every 3 months, with some additional secondary outcomes and covariates collected at six-month intervals. Annual comprehensive surveys are conducted in-person at enrollment, 1 year (point of cross-over) and 2 years. The annual survey will assess primary and secondary outcomes as well as covariates. Brief 3-month surveys are completed online and focus on primary outcomes and any change in demographics, such as living situation. Links for the brief 3-month surveys are sent by SMS or email, depending on participant preference, up to four times within a 10-day window, with a final personalized reminder sent 1 day before the link expires. All surveys–both comprehensive and brief–are collected in REDCap by CAPI (Computer-assisted personal interviewing) in order to ensure privacy and consistency in data collection. Soft credit checks require an additional consent and are performed to assess participants’ baseline credit scores, following enrollment, and again at 6 and 12 months. Participants are remunerated for all surveys via their preferred form of payment (CashApp or gift card). Centering BEA needs and preferences, payment options were determined in consultation with BEA and the CWG.

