### Measures

#### Exposure

The primary exposure is intervention arm assignment (see all measure in Table 1). Secondary exposure variables include: receipt of financial mentoring (yes/no) and participation in peer discussion groups (yes/no) during each 3-month study interval. Because engagement with any treatment option will vary by individual, we will also capture intervention dose (e.g., mentoring sessions attended) on study monitoring forms.

**Table 1 tab1:** Study measures: domains, instruments, and time points.

Domain	Instrument/measure	Data source and frequency
Primary exposure		
Intervention	Randomization arm (GI receipt in phase I or phase II)	Study records
Primary outcomes		
Financial well-being	Investments in future (Enrollment in education/training)	Quarterly surveys
Mental Health	CESDR-10: major or probable major depressive episode (64, 65)	Quarterly surveys
Unmet need for health services	Unmet need for mental health services	Quarterly surveys and monthly brief check-ins
	Unmet need for sexual and reproductive health services	Quarterly surveys and monthly brief check-ins
Secondary outcomes		
Financial well-being	Savings, Debt	Surveys at baseline, 6, 12, 18, 24 months
	Credit score	Assessed at baseline, 6, and 12 months
	Financial Capability (knowledge, skills, practices, mindset) (45)	Every six months: baseline, 6, 12, 18, 24 months
Mental health	Anxiety – moderate–severe: score ≥ 10 on GAD-7 (66, 67)	Quarterly surveys
	Hope/ future orientation (68, 69)	Surveys at baseline, 6, 12, 18, 24 months
Physical health	General health (70); fatigue	Surveys at baseline, 6, 12, 18, 24 months
Secondary exposure		
Intervention dose	Engagement with optional intervention components (peer groups and mentoring)	Study monitoring forms
Covariates/Mediators		
Demographics	Age, gender identity, housing/living situation, household membership, income, employment	Quarterly surveys
Strengths and assets	Resilience (71); self-esteem; Black identity (72); decision-making and goal-setting	Frequency varies – six-month and annual surveys
Social and structural contextual factors	Experienced discrimination (73); alcohol and substance use (74); social support (75, 76); social cohesion (77, 78); incarceration; relationship violence (79); trauma (80); prosocial involvement; food security	Frequency varies - quarterly; six-months; and annual surveys

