### Analyses

#### Preliminary analyses

Frequency tables for all categorical variables and measures of central tendency and variability for continuous variables (e.g., average monthly income, age) will be used to characterize the sample and check for imbalances between the randomization arms. If arms differ significantly at baseline on one or more covariates or if imbalances in arms occur due to differential loss to follow-up, we will use causal modeling methods (e.g., inverse probability weighting, targeted maximum likelihood estimation) to balance distributions and obtain the desired marginal effect estimates under the counterfactual assumption of balanced arms (85–89). We will address incomplete data with multiple imputation (90). SAS will be used for analyses.

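### The credit score labelled baseline is taken after participants know their arm, under a separate consent of unstated timing, so the credit-score subset may not be protected by randomisation

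*Protocol article*

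**What the plan says.** Four statements in the protocol article bear on this point.

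- **Disclosure of arm** (Randomization and treatment allocation): "Study staff inform participants of group assignment during the enrollment appointment, following baseline survey completion". The same section says that "blinding the participants and study staff is not possible".
- **Credit checks** (Structured surveys): "Soft credit checks require an additional consent", and they provide "baseline credit scores, following enrollment, and again at 6 and 12 months". Nothing says whether this consent is signed before or after the arm is disclosed.
- **Schedule** (Table 1): credit score is "Assessed at baseline, 6, and 12 months". Savings and debt, in the row above, have "Surveys at baseline, 6, 12, 18, 24 months", and financial capability also runs to month 24.
- **Missing data and imbalance** (Preliminary analyses): "We will address incomplete data with multiple imputation". Inverse probability weighting or targeted maximum likelihood is to be used if the arms differ at baseline or become unbalanced through differential loss to follow-up.

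Credit score is a secondary financial outcome. The article also names credit as a possible mediator in its exploratory analyses.

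**The concern.** Randomisation makes the two arms of 150 comparable as whole groups. It does not do so for a subset formed after people learn their arm. The credit-score sample consists of those who agree to an extra, optional check. Someone who has just heard that $500 a month starts now may answer that request differently from someone told to wait a year, and the staff who handle enrollment also know the arm. If agreement depends on both arm and creditworthiness, the arms' credit scores can differ with no effect of guaranteed income.

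The label matters too. A reader of Table 1 would take a baseline value to precede allocation, and would use it both to judge balance and as the starting point for change. This value precedes neither allocation nor its disclosure.

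**Working it through.** **1. Order of events.** Putting the two sections together gives: baseline survey, then disclosure of arm (both at the enrollment appointment), then the first credit check (after enrollment), then checks at months 6 and 12. The article words the annual survey as taking place at enrollment and the credit check as coming after it. It uses the same after-enrollment phrase for the first qualitative interview, which it places within two months of enrollment. The natural reading is that the first score post-dates disclosure. The position of the credit consent in this sequence is not given.

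**2. What follows from the consent timing.**
- Signed before disclosure: agreement cannot depend on arm, and the consenting subset stays randomised. Only the label is wrong.
- Signed after disclosure: agreement may depend on arm, and the subset is not protected.

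**3. Scale of a level difference (illustration).** The article gives no credit consent rate and no power figure for credit, so there is nothing to reproduce. Assume a standardised score with correlation r to willingness to consent, and let c be the consent rate. The mean score among consenters is then r × φ(t)/c, where φ is the standard normal density and t the normal quantile at 1 − c. The values of φ(t)/c are:
- c = 0.90: 0.1755/0.90 = 0.195
- c = 0.80: 0.2800/0.80 = 0.350
- c = 0.70: 0.3477/0.70 = 0.497

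Absolute gap between arms in SD, which is r times the difference of two such values:

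| Consent, GI arm / waitlist arm | r = 0.1 | r = 0.5 |
|---|---|---|
| 90% / 90% | 0 | 0 |
| 90% / 80% | 0.1 × 0.155 = 0.02 | 0.5 × 0.155 = 0.08 |
| 90% / 70% | 0.1 × 0.302 = 0.03 | 0.5 × 0.302 = 0.15 |

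For comparison, take 150 per arm, the article's 25% attrition, and assumed consent of 100% down to 60%. That leaves 150 × 0.75 × 1.0 = 112.5 or 150 × 0.75 × 0.6 = 67.5 per arm. The difference detectable with 80% power at two-sided 0.05 and a single time point is (1.96 + 0.84) × √(2/n), which is 0.37 and 0.48 SD respectively.

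**4. What differencing does.** The article's between-arm method is difference-in-differences by GEE (Primary analyses), with continuous GEE for continuous measures (Secondary analyses). Suppose 60% consent whatever their arm, with mean score 600, and a further 5% to 20% consent only if given the income now, with mean 540. All of these are assumptions. The GI-arm mean is (0.60×600 + 0.05×540)/0.65 = 595.4, or (0.60×600 + 0.20×540)/0.80 = 585.0, against 600 in the waitlist arm: a gap of −4.6 to −15 points. If both kinds of consenter change alike, that gap is present at the first check and at month 12, and the difference-in-differences is 0. If the extra consenters change by δ points more than the others for reasons unrelated to the income, the bias is their share times δ: 0.05/0.65 = 0.08δ, up to 0.20/0.80 = 0.25δ. The documents give no basis for a value of δ.

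**5. Schedule.** Month 12 is the crossover point. Of the three credit scores, none falls after month 12. None therefore lies within the waitlist arm's income year or after the Phase 1 arm's payments end.

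**The case against.** The strongest reply is that the harm rests on something the article does not say. The order in which forms are signed at a visit is detail that a condensed article leaves to the full protocol. A credit score is not self-reported, so knowing one's arm cannot colour the value. Differencing removes a stable gap. The planned weighting methods could use the baseline survey, which is completed before disclosure.

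Much of this stands. A reader might infer that the credit comparison is biased, or off by 5 to 15 points. The documents do not support that: the consent timing is unknown, the inputs are invented, and the raw gap cancels under the planned analysis unless the two kinds of consenter change differently. A reader might also infer that the first score already reflects a payment. Deposits are made on the first of the month, but no interval between enrollment and the check is given, so this cannot be concluded.

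Nor is ending credit at month 12 an error. Structured surveys and Table 1 agree on it, the randomised 12-month contrast is unharmed, and hypotheses H3 and H4 do not name credit. Savings, debt and financial capability do cover the waitlist arm's income year.

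Two things remain. The score called baseline follows disclosure on the article's own wording. And the triggers for weighting do not name refusal of credit consent, while multiple imputation would not repair refusal that depends on arm and on the unseen score.

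**Conclusion.** The point holds in a limited form. The baseline credit score is taken after the arm is known, and its separate consent has no stated place in the sequence. If that consent follows disclosure, the credit-score subset may differ by arm and is not protected by randomisation. If it precedes disclosure, only the label needs correcting.

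The size cannot be derived from the documents. Under the assumptions shown, a level gap of 0.02 to 0.15 SD is possible, against a detectable difference of 0.37 to 0.48 SD. Differencing removes such a gap when it is fixed and leaves whatever part comes from differential change. One secondary outcome and an exploratory mediator are affected. No primary outcome, sample size or primary test changes.

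Separately, the Introduction and Trial design offer the study as evidence on outcomes after payments end, without excepting credit. For credit that evidence will not exist, and this limits what may be claimed.

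**What to change.** - **Participants still to be enrolled:** obtain the credit-check consent and run the first soft check before the arm is disclosed, alongside the baseline survey. The cost is reordering steps within one visit.
- **Participants already enrolled:** report credit consent by arm together with baseline survey characteristics. Add a sensitivity analysis that weights for consent using the survey data collected before disclosure. Do not describe the score as a pre-allocation baseline. Restricting the analysis to people who consented before disclosure would not help: if consent was sought afterwards that group is empty, and if it was sought beforehand the restriction is unnecessary. The cost is analysis and reporting text.
- **Scope:** state that credit score informs only the 12-month comparison and does not contribute to conclusions on sustained effects. This is a sentence of wording. Checks at 18 and 24 months would be an optional extension, not a needed correction.
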